### Study objectives

The primary objective of the study is to assess the incidence and risk factors of post-COVID-19 condition in a cohort of recovered COVID-19 patients.

The secondary objectives of the study are as follows:To evaluate the association between circulating SARS-CoV-2 variants and the risk of post-COVID-19 condition.To identify different clinical phenotypes of post-COVID-19 condition.To evaluate the long-term residual organ impairment, specifically of the lung, heart, central nervous system, and peripheral nervous system, in relation to patient demographic and clinical characteristics such as age, gender, comorbidities, severity of disease, and virology including viral variant, specific mutations, and viral load in the acute phase.To compare the incidence of post COVID-19 condition between males and females.

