### Study design

This is an observational retrospective and prospective, multicentre, cohort study. The study will last for 3 years, from February 2022 to February 2025.

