### Data collection

During the acute phase of COVID-19 disease, data collection involves gathering demographic, clinical, and viro-immunological data. Subsequently, data collection is requested at each follow-up time point. To facilitate this process, a specially designed data management suite has been implemented. It incorporates a security-focused architecture that enables manual data entry into case report forms and secure file transfer for bulk data uploads. This flexible approach accommodates the various data infrastructures employed by the participating centres, whether they collect data from databases or manually. All data is meticulously curated and consolidated within a centralised relational database.

Data collection procedures strictly adhere to the established protocol, the most recent version of the Declaration of Helsinki, the International Conference on Harmonization Good Clinical Practice (ICH-GCP) or ISO EN 14155 guidelines, the regulation 2016/679 GDPR, as well as all relevant national legal and regulatory requirements.

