### Data analysis

The study data will be presented as absolute numbers and percentages for categorical data, median and Interquartile Range or mean and standard deviation for quantitative variables. The incidence of post-COVID-19 condition will be calculated, and comparison between groups based on exposure factors of interest will be performed using appropriate statistical tests such as Student t-test or Mann Whitney and Chi-square test. Predictors of post COVID-19 condition will be investigated by fitting a univariable and multivariable logistic regression analysis which will be adjusted for possible confounders.

Due to potential losses to follow-up, not all hospitalised COVID-19 patients and patients diagnosed with SARS-CoV-2 infection will attend the post COVID-19 visit. This may result in a non-representative sample, potentially leading to collider bias and distorting the estimation of the effect of an exposure of interest. This bias can be addressed for hospitalised patients by using Inverse Probability Weighting through the creation of a pseudo-sample where individuals are weighted according to the inverse of the probability of being sampled for the post COVID-19 visit. A multivariable logistic regression model will be fitted to estimate the probability of COVID-19 hospitalised individuals to be included in the post COVID-19 cohort based on their characteristics (propensity score, PS), and weights inversely proportional to this probability will be generated (1/PS). Weighted logistic regression analyses will then be used to investigate predictors of post COVID-19 condition. Missing data will be handled using the missing “indicator method,” or alternatively using multiple imputations technique.

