The sample size calculation will be determined by the number of expected events in the follow-up period. Based on the currently available data, we estimated an incidence of WHO post COVID-19 condition of 54% (95%CI 45–69%). We will use the comparison between the risk of developing post-COVID-19 condition in participants infected with the Delta versus Omicron viral variant of concern (VoC) for the sample size calculation. According to recent analysis, after controlling for vaccination and other confounders, the risk of hospitalisation comparing Omicron versus Delta variant ranged between 0.55 and 0.88 [21]. Our assumption is that if post COVID-19 condition occurs due to the direct effects of the virus (e.g., through disease severity, level of hyper-inflammation, or other), a similar difference could be seen when comparing the long-term risk of developing post COVID-19 condition by VoC. The cohort of 2,300 participants, accounting for 35% of follow-up, will still guarantee 90% power to detect a reduction in the risk of post-acute sequelae of at least 25% comparing participants infected with Omicron vs. Delta variants.

Data handling and statistical analyses will be performed by the team of statisticians and Artificial Intelligence experts in WP5. Python computing will be used for executing the statistical analysis.

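### The missing-indicator method is named first for missing data, and in this non-randomised cohort it leaves part of the confounding by any incomplete confounder in the adjusted odds ratios

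*Protocol article*

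**What the plan says.** The Study design section is plain about the type of study: "This is an observational retrospective and prospective, multicentre, cohort study". The Data analysis section of the Protocol article then relies on covariate adjustment: "Predictors of post COVID-19 condition will be investigated by fitting a univariable and multivariable logistic regression analysis which will be adjusted for possible confounders". A weighting step follows for hospitalised patients who do not attend the post-COVID visit, after which "Weighted logistic regression analyses will then be used to investigate predictors of post COVID-19 condition".

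The paragraph closes with the only statement on missing data: "Missing data will be handled using the missing “indicator method,” or alternatively using multiple imputations technique". It does not say which variables are meant, what missingness assumption is made, or when the second method replaces the first.

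Two other places bear on the point. The first secondary objective is "To evaluate the association between circulating SARS-CoV-2 variants and the risk of post-COVID-19 condition", and the Omicron-versus-Delta comparison is also the basis of the sample size. The Data collection section says that the system accommodates centres "whether they collect data from databases or manually", so covariates come from unlike sources and partly from retrospective records.

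**The concern.** Indicator coding sets an incomplete covariate to a constant where it is missing and adds a dummy variable for missingness. Among patients coded as missing, the exposure and outcome are then compared without adjustment for that covariate. One exposure coefficient is fitted to everyone, so it lands between the adjusted and the crude value. Randomisation would make the crude and adjusted comparisons agree in expectation apart from non-collapsibility. Here exposure is not randomised, and adjustment is what is meant to remove confounding.

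At stake are the risk-factor odds ratios, which are half of the primary objective, and the variant comparison. Vaccination is a natural example: the sample-size text itself notes that the cited Omicron-versus-Delta analysis of hospitalisation controlled for it. If vaccination lowers the risk of post-COVID-19 condition and is commoner among Omicron cases, the confounding left over pushes the Omicron odds ratio below its true value. That is the direction which the Study hypotheses section expects, so an artefact could pass for confirmation.

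**Working it through.** The article gives no figure for missing data, so there is none of its own to reproduce. The check asks how far the indicator-method OR moves from a known true value.

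**Inputs from the article.** Observational design; logistic regression adjusted for confounders; 2,300 participants; an expected incidence of 54%; a 25% reduction as target. Reading the 35% in the sample-size text as loss leaves 2,300 × 0.65 = 1,495.

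**Inputs assumed.** Missing share, confounder strength and exposure–confounder association. None is in the article, so ranges are used. Values are missing completely at random throughout, which is the most favourable case.

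**Large-sample check, vaccination as confounder.** X = Omicron (half of the cohort), V = vaccinated, and logit P(Y) = log(1.5) + 0·X + log(OR of V)·V, so the true variant OR is 1.00. The indicator model regresses Y on X, V set to 0 where missing, and the missingness dummy. Models were fitted to exact cell probabilities, so there is no simulation noise.

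The crude OR for the strongest scenario can be done by hand. Risk is 1.5/2.5 = 0.600 if unvaccinated and 0.75/1.75 = 0.429 if vaccinated.
- Delta (30% vaccinated): 0.7 × 0.600 + 0.3 × 0.429 = 0.549.
- Omicron (80% vaccinated): 0.2 × 0.600 + 0.8 × 0.429 = 0.463.
- Crude OR = (0.463/0.537)/(0.549/0.451) = 0.71, against a true 1.00.

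Indicator-method OR by missing share:

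| Vaccinated, Omicron vs Delta | OR of V | Crude OR | 5% | 10% | 20% | 30% |
|---|---|---|---|---|---|---|
| 80% vs 30% | 0.5 | 0.709 | 0.977 | 0.956 | 0.916 | 0.881 |
| 80% vs 30% | 0.75 | 0.866 | 0.991 | 0.982 | 0.965 | 0.949 |
| 80% vs 60% | 0.5 | 0.872 | 0.993 | 0.985 | 0.971 | 0.958 |
| 80% vs 60% | 0.75 | 0.945 | 0.997 | 0.994 | 0.988 | 0.982 |

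At 40% missing the first row falls to 0.849. Full-data and complete-case fits give 1.000 in every cell.

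**Share of confounding left** = log(indicator OR)/log(crude OR) when the true OR is 1.00. First row, 20% missing: log(0.916)/log(0.709) = 0.255. Last row, 20% missing: 0.21. First row, 30% missing: 0.37. The share left is close to the missing share and somewhat above it when confounding is strong.

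**With a real effect.** A 25% reduction from 54% is 0.54 × 0.75 = 40.5%, so OR = (0.405/0.595)/(0.54/0.46) = 0.58. In the strongest scenario at 30% missing, the indicator method gives 0.514.

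**Finite-sample check at n = 1,495, true OR 1.00, two-sided 5% test.** A separate set-up was used: confounder prevalence 40%, with 600 runs for the indicator method and 150 runs of 10 imputations each for multiple imputation.

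| Confounder–outcome OR; confounder–exposure OR | Missing | Indicator: mean OR, rejection | Multiple imputation: mean OR, rejection |
|---|---|---|---|
| 2; 0.5 | 20% | 0.97, 6% | 1.00, 4% |
| 3; 0.33 | 20% | 0.94, 10% | 0.99, 7% |
| 2; 0.5 | 35% | 0.95, 10% | 1.00, 6% |
| 3; 0.33 | 35% | 0.90, 15% | 1.00, 5% |

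The imputation model contained exposure and outcome. With 150 runs, its rejection rates carry about ±3.5 percentage points and are compatible with 5%. The 6% for the indicator method is also not clearly above 5% with 600 runs.

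**The case against.** The strongest reply is that the size of the harm cannot be known from the article, and that it may be small. This stands. With few missing values or weak confounding the bias is negligible: 0.997 at 5% missing in the mildest scenario, and 0.977 even in the strongest. Only confounders with missing values are concerned.

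Several stronger readings are tempting, and the article does not support them.
- A reader might infer that confounding is left wholly in place. It is left in part, roughly in proportion to the missing share.
- A reader might infer that vaccination data will be incomplete. Table 1 schedules vaccination status at T1, T2 and T3, and the Discussion says that it is collected by questionnaire. Retrospective participants may have gaps, but no share is given, and the Data analysis section names no confounder. Vaccination serves here only as an illustration.
- A reader might count missing virology as an example. In the Omicron-versus-Delta contrast variant is the exposure, and a missing exposure is a different problem which these calculations do not address.
- A reader might infer that the method will be picked after the results are seen. The article has no selection rule, but a condensed article may leave that to an analysis plan. The silence shows an open choice and no more.

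It can also be said that multiple imputation is already in the sentence, and that complete-case analysis is unbiased in these scenarios too. Both are true. The second depends on values being missing completely at random, which the article does not claim, so it supports complete-case analysis as a sensitivity analysis. The first makes the change cheap. It does not cure the order of preference, because an analyst who follows the sentence as written starts with the indicator method. Nor does the weighting step help: it concerns attendance of hospitalised patients and does not fill in missing confounder values.

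**Conclusion.** The point holds in limited form. The article names a method that is unsuitable for incomplete confounders in a non-randomised cohort, and names it first and without restriction. This is a stated choice, not a detail left to another document. Followed as written, it draws the exposure OR from the adjusted towards the crude value even when data are missing completely at random.

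The size is an assumed range. With a true OR of 1.00 and 20% missing, the indicator-method OR runs from about 0.99 (80% vs 60% vaccinated, vaccination OR 0.75) to about 0.92 (80% vs 30%, OR 0.5). At 5% missing it runs from about 1.00 to 0.98. These figures assume one binary confounder, values missing completely at random and a logistic model without interaction.

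The adjusted risk-factor and variant estimates are exposed to this. The incidence estimate is not affected by this mechanism, because it does not come from covariate adjustment.

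**What to change.** Reword the missing-data sentence in the Data analysis section of the Protocol article.
- Make multiple imputation the primary method for incomplete confounders. The imputation model should contain the outcome, the exposure, the covariates of the analysis model, centre, calendar period and the variables that predict attendance in the weighting model.
- Remove the indicator method as a primary option. If it is kept at all, label it a sensitivity analysis.
- Add a complete-case analysis as a sensitivity analysis; the article does not plan one at present.

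The number of imputations and the pooling rules can stay in the analysis plan. The cost is a change of wording plus modest extra analysis work and computing time. No further data collection is needed, and the method promoted is one that the article already names.

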## Possible study strengths and limitations

The strengths of this medical study include its international cohort of patients who will be followed-up for one year after acute infection. The study also collects a comprehensive list of symptoms and objective measures of symptoms, such as dyspnoea, fatigue, and psychological issues, through standardised questionnaires and scales. Additionally, blood samples will be collected during the acute phase and follow-up for future studies on possible pathogenetic mechanisms of post COVID-19 condition.

However, there are also some potential limitations of the study to consider. One possible limitation is the risk of selection bias, as patients without ongoing symptoms may not keep follow-up appointments, leading to losses in follow-up, despite some statistical methods could be used to handle this bias. Another possible limitation is the potential overestimation of post COVID-19 condition due to the WHO definition, which includes any kind of symptom.

## Data dissemination

The results of this study, regardless of whether they are positive, negative, or inconclusive, will be published in peer-reviewed journals and/or presented at national and international conferences. Open access journals will be given preference for publication. All publications and presentations will be listed on the EuCARE webpage.

## Discussion

The EuCARE project comprises several patient cohorts and schools that provide an advanced response to COVID-19 epidemics. The EuCARE-POSTCOVID study is responsible for investigating the characteristics of the post COVID-19 condition, which seems to affect up to 10–15% of patients, according to a recent review [22]. Despite the current reduction in the incidence and severity of acute SARS-CoV-2 infections in Europe, the post-COVID-19 condition remains a medical challenge. The clinical course of the syndrome, its possible risk factors, and the best diagnostic-therapeutic approach are not yet entirely understood. First data shows that the symptoms could last for one year or more.

A large group of definitions has been proposed and adopted by different research groups to indicate the failure to return to a pre-COVID state of health. We will use the 2021 definition of post-COVID-19 condition identified by the WHO because it appears to be the most standardised and globally applicable definition so far. This definition will allow us to compare our data with those of other similar cohorts [13, 16, 23, 24]. Since the WHO definition includes any symptoms that don't have an alternative diagnosis, it is quite nonspecific and could cause an overestimation of COVID-19 sequelae. We will also focus on possible clusters of symptoms identifying phenotypes of post-COVID-19 condition. This study will focus on understanding the incidence and predictors of post-COVID-19 syndrome by comparing the different pandemic waves, thanks to the long duration of the study and the possibility of including retrospective data from the beginning of the epidemics.

Among predictors, the association between gender and post-COVID-19 syndrome will be explored. Our preliminary data and previous cohorts have underlined a possible higher prevalence of the condition in females, though the reason for this association is not known [13].

The comprehensive questionnaires for symptom collection and the scales for the objective and standardised measure of symptoms such as dyspnoea, fatigue, and psychological issues (anxiety, depression, PTSD, and health-related quality of life) will be repeated at different time points, allowing us to understand the duration and evolution of symptoms over time. Through questionnaires, data about vaccination against SARS CoV-2, reinfections, and new health problems requiring hospital admission or new diagnosis after COVID-19, such as the new onset of diabetes or other health conditions, will be collected.

The collection of biological samples will allow future studies on pathogenetic mechanisms of post-COVID-19 sequelae, such as persistent or excessive inflammation, immune dysregulation, or viral reservoirs.

The strengths of this study protocol are the inclusion of several cohorts outside Europe and the long study period that allows a clear and wide overview of the post COVID-19 condition. We also need to recognise that the study has some limitations, as already stated. Possible solutions to overcome these limitations could be the use of statistical methods such as propensity score matching to address biases due to losses of follow-up. The telehealth approach that is currently being implemented at the coordinating centre for performing post-COVID-19 evaluations without coming to the hospital could reduce losses to follow-up.

In conclusion, the EuCARE-POSTCOVID Study is an international multicentre cohort study that aims to better define and characterise the post COVID-19 condition over the different pandemic waves. The comprehension of the current epidemiology, predictors, clinical manifestations, and pathogenetic mechanisms of this syndrome is crucial in delineating the best management and therapeutic approaches that could improve patients' quality of life.

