### Patient assessment and follow-up protocol

The patient assessment and follow-up protocol for acute COVID-19 disease involves follow-up visits at 2–3, 6–9, and 12–15 months after clinical recovery. At each visit, routine blood exams and medical visits will be conducted, along with several assessments via questionnaires, including the short version of the post COVID-19 WHO Case Report Form (WHO CRF) for collection of symptoms and newly emerged complaints after COVID-19, the Fatigue Numerical Rating Scale, the Medical Research Council (MRC) dyspnoea scale, the 5-level EQ-5D test (EQ5D-5L), the 12-item WHO Disability Assessment Schedule (WHODAS), the Montreal Cognitive Assessment (MOCA), the Hospital Anxiety and Depression Scale (HADS-A/D), and a screening tool named PCL-5 for Post-Traumatic Stress Disorder (PTSD). If patients are unable to attend the post-COVID-19 clinic, the questionnaires will be able to be completed through a phone interview. All questionnaires will be standardized and available in multiple languages (Fig. 1).

Further instrumental diagnostic evaluations such as diffusing capacity of lung carbon monoxide (DLCO), spirometry, lung computed tomography (CT) scans, pneumological evaluation, echocardiography, cardiological evaluation, neurological evaluation, rehabilitation medicine specialist examination, and psychological evaluation will be conducted as necessary.

Pulmonary symptoms are common after the acute phase, thus patients undergo the MRC dyspnoea scale and oxygen saturation measurement at each post-COVID visit. Further evaluations such as chest CT scans, diffusing capacity of lung carbon monoxide (DLCO), spirometry, and a complete pneumological evaluation will be performed if oxygen saturation is < 95% or MRC dyspnoea scale grade is 2–5.

Patients who recovered from acute COVID-19 disease could present a higher risk of cardiac diseases, including heart failure, myocardial infarction, and arrhythmia in the mid- and long-term [18]. During the scheduled post-COVID visits, patients undergo a complete medical examination, including heart rate and blood pressure measurement, and fill in the MRC dyspnoea scale. Further evaluations such as an electrocardiogram, a cardiologic visit, and an echocardiography will be performed as necessary.

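### The only attrition weight described covers hospitalised patients' entry to the cohort, so it leaves symptom-dependent loss between the three visits uncorrected and gives outpatients no weight

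*Protocol article*

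**What the plan says.** **Repeated measurement.** The section on patient assessment and follow-up schedules "follow-up visits at 2–3, 6–9, and 12–15 months after clinical recovery". Table 1 places the symptom form and the fatigue, dyspnoea, quality-of-life, cognitive, psychological and disability instruments at all three visits. The Discussion presents this repetition as "allowing us to understand the duration and evolution of symptoms over time", and the Abstract makes the same promise.

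**Expected loss.** Under strengths and limitations the article warns that "patients without ongoing symptoms may not keep follow-up appointments, leading to losses in follow-up". It gives no rates by visit or by symptom status.

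**Stated correction.** The Data analysis section says: "This bias can be addressed for hospitalised patients by using Inverse Probability Weighting". A logistic model is fitted "to estimate the probability of COVID-19 hospitalised individuals to be included in the post COVID-19 cohort based on their characteristics", and each patient is weighted by "the inverse of the probability of being sampled for the post COVID-19 visit". The use of the weight is then fixed: "Weighted logistic regression analyses will then be used to investigate predictors of post COVID-19 condition".

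**Other measures.** The same section names the missing-indicator method or, as an alternative, multiple imputation. Elsewhere the article allows questionnaires by phone, mentions a telehealth approach at the coordinating centre, and offers propensity score matching as a possible answer to loss.

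**The concern.** The article names a loss mechanism driven by symptoms, describes a correction for a different step, and still expects to learn how symptoms evolve.

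The weight deals with one event, entry to the cohort. To fit that model, the same variables are needed for patients who entered and for those who did not. Symptoms recorded at follow-up exist only for those who entered, so they cannot be in it. Whether a patient seen at T1 comes back at T2, and again at T3, is not modelled. Outpatients (Group 2) have no weight at any step.

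If patients who have recovered stop coming, those still seen at 6–9 and 12–15 months are increasingly the ones who are still ill. Percentages among attenders then overstate how many patients remain symptomatic. This is the quantity behind any statement about duration.

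**Working it through.** The article gives no figure for retention by symptom status or for prevalence at T2 and T3, so there is none to reproduce. Its power statement is not in question here.

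**Inputs**
- Prevalence at T1: 54%, the incidence in the sample-size paragraph. Using it as T1 prevalence is an assumption.
- Overall retention at T3: about 65%. This reads the 35% in the sample-size paragraph as loss. The wording there is ambiguous, and the figure serves only to keep the scenarios realistic.
- Retention per step, *a* for symptomatic and *b* for symptom-free patients: assumed and varied.
- Dropout is permanent, and return depends on status at the preceding visit.
- Entry to the cohort depends only on a baseline variable that the inclusion weight captures. This favours the plan, because the single weight is then exactly right at T1.

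**1. No true change.** Prevalence among attenders after *k* steps is 0.54·aᵏ / (0.54·aᵏ + 0.46·bᵏ).

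With a = 0.87 and b = 0.72:
- T2: 0.4698 / (0.4698 + 0.3312) = 58.7%
- T3: 0.4087 / (0.4087 + 0.2385) = 63.2%, with 0.4087 + 0.2385 = 64.7% retained

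Dividing each T3 term by its own retention (0.7569 and 0.5184) gives back 0.54 and 0.46. Attendance weights based on preceding status therefore return 54% at every visit. A simulation of 2 million patients agreed: 54.0 / 58.7 / 63.2% with the single inclusion weight, and 54.0% throughout with visit-specific weights.

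**2. Sensitivity to the retention ratio.** Only r = b/a matters: T2 = 0.54/(0.54 + 0.46r) and T3 = 0.54/(0.54 + 0.46r²).

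| r | T2 | T3 |
|---|---|---|
| 1.0 | 54.0% | 54.0% |
| 0.9 | 56.6% | 59.2% |
| 0.8 | 59.5% | 64.7% |
| 0.7 | 62.6% | 70.6% |
| 0.6 | 66.2% | 76.5% |

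The excess at T3 runs from 0 points with equal retention to 22.5 points at r = 0.6.

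**3. True decline.** Let 20% of symptomatic patients recover at each step. True prevalence is then 54.0%, 0.54 × 0.8 = 43.2%, and 0.432 × 0.8 = 34.6%. Results with the single inclusion weight:

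| Retention per step | T1 | T2 | T3 |
|---|---|---|---|
| 80% vs 80% | 54.0% | 43.2% | 34.5% |
| 87% vs 72% | 54.0% | 46.9% | 41.3% |
| 90% vs 60% | 54.0% | 51.0% | 48.8% |

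These are simulated, so 34.5% in the first row matches the truth within simulation error. Visit-specific weights recovered the true series to within 0.1 point. In the lower two rows the observed series still falls, but too slowly.

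**4. If attendance depends on current symptoms.** Keep the decline and 87% vs 72%, but let T2 attendance follow T2 status. Attenders are then 0.432 × 0.87 = 0.3758 symptomatic, 0.108 × 0.72 = 0.0778 newly recovered, and 0.46 × 0.72 = 0.3312 symptom-free since T1.
- Without an attendance weight: 0.3758 / 0.7848 = 47.9%.
- With weights from T1 status, the attendance of those symptomatic at T1 is (0.3758 + 0.0778)/0.54 = 0.84, and the estimate is 0.3758/0.84 = 44.7%.
- The truth is 43.2%. Weights from the preceding visit cut the error from 4.7 to 1.5 points but do not remove it.

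**The case against.** The best case for the plan is that this is a condensed article. A longitudinal model is commonly left to the full protocol or SAP, and the sentence on symptom evolution is in the Discussion, not among the listed objectives. The analysis section speaks of incidence and predictors and does not claim to estimate trajectories. The bias is already declared as a limitation. Multiple imputation could use earlier visits under missing at random, which is the same assumption that attendance weights need. Phone interviews and telehealth may reduce loss. The symptom form also records symptoms that have since resolved, so a later visit can partly fill an earlier gap.

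Much of this stands. The absence of a longitudinal model is not a finding by itself. A reader might infer that the plan compares percentages visit by visit, but the text does not say so: the named tests compare exposure groups. A reader might also infer that prevalence will drift upward. The article says only that symptom-free patients may miss appointments.

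What does not stand is the idea that the named measures close the gap. The missing-indicator method cannot supply an unobserved outcome. Imputation is an unspecified alternative to it. Matching is only a possibility, with no attendance model by visit. Phone contact and telehealth may shrink the loss but do not correct what remains. A later questionnaire helps only for patients who return.

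**Conclusion.** The point holds in conditional form. The correction that the article fixes addresses a different step from the loss that it expects, and it omits outpatients. If symptom-free patients return less often, prevalence at T2 and T3 among attenders is biased upward relative to the truth, and persistence is overstated. With 87% vs 72% retained per step, the T3 excess is about 9 points when true prevalence is constant (63.2% vs 54.0%) and about 7 points when it falls (41.3% vs 34.6%).

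These sizes rest on assumed retention rates, on 54% as T1 prevalence, and on permanent dropout. With equal retention there is no bias. The documents do not support the stronger statement that the observed series must rise: where symptoms truly resolve, it can still fall, only too slowly.

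**What to change.** 1. For hospitalised patients and outpatients alike, model attendance at T2 and at T3 from baseline characteristics plus symptoms and scores at the preceding visit. Multiply these visit-specific weights by the inclusion weight where one exists, and use them in a repeated-measures analysis with robust variance. Alternatively, use multiple imputation or a mixed model that includes earlier-visit symptoms.
2. State that the missing-indicator method will not be used for outcomes at missed visits.
3. Add a missing-not-at-random sensitivity analysis, because attendance may depend on current symptoms.
4. Report duration and evolution from this analysis, not from percentages of attenders.

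No new data are needed, since symptoms and scores are already scheduled at every visit. The cost is more modelling and somewhat wider intervals at T2 and T3.
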